## Abstract

**Background:**

Current evidence suggests that the incidence of cancer is low in vegan populations, and experimental studies have revealed a significant role of dietary proteins in cancer development and progression. However, little data currently exists regarding the effect of a plant-based diet on the progression of diagnosed cancer.

**Objective:**

The main objective of this study is to determine if a reduction or total elimination of animal protein from the diet can positively influence the outcome of an existing cancer and, in addition to standard oncological therapies, increase remission rates.

**Methods:**

The primary aim of this online study is to test the effect on remission rates in cancer patients (primary outcome) with distinct self-selected dietary patterns (omnivore, lacto-ovo-vegetarian, vegan), and allow for an estimation of the effect size. Secondary outcomes are tumor behavior, relapse-free interval, therapies, therapy tolerability and side-effects, comorbidities, medication, quality of life, acceptance, and feasibility of the selected diet. Safety concerns exist for vegan diets (especially in cancer patients) and the study will carefully monitor for deterioration of health, tumor progression, or malnutrition. Furthermore, the study will evaluate the online portal as a study platform (technical and safety aspects, and sequence of displayed questionnaires) as well as the validity of self-reported and online-generated data.

**Results:**

The study was performed between April, 2015 and June, 2016, and a preliminary evaluation of safety aspects was undertaken after June, 2016. Primary and secondary outcomes will be evaluated when the final patients complete the study in December, 2016.

**Conclusions:**

This study will reveal information about the effects of dietary patterns on cancer disease and progression. The methodology of the study addresses several aspects and limitations of nutrition studies in cancer patients, such as precision of nutrition data, acceptance criteria, online methodology, and safety aspects.

**ClinicalTrial:**

Clinicaltrials.gov NCT02437474; https://clinicaltrials.gov/ct2/show/NCT02437474 (Archived by WebCite at http://www.webcitation.org/6jL7UUCVq)

## Introduction

Every year, cancer is diagnosed in 14.1 million people worldwide, and 8.2 million people die from this disease. These figures represent 13% of all deaths around the world, and malignant tumors are one of the main causes of death in industrialized countries [1]. The prognosis for the future is even worse, with a 70% increase in cancer incidence expected, meaning 22 million new cases will be diagnosed every year over the next twenty years [1]. The most common types of cancer for men are lung, prostate, and colorectal cancer (CRC), while women mostly suffer from breast, colorectal, and lung cancer [1].

Cancer is known to be a multifactorial disease with many external risk factors that need to be considered, especially lifestyle factors. In recent years, nutrition has been highlighted as a key risk factor, and is now considered to be responsible for 30% of all cancer cases in industrialized countries [2]. Different nutritional aspects have been implicated in the stimulation of a large number of cancers. Alcohol is known for its connection to liver cancer, but high body mass index (BMI) and obesity also play a major role in cancer development [3-5]. While these factors primarily affect industrialized countries, cancer in developing countries is often linked to micronutrient deficiencies [6].

Other cancer risk factors include food that has been prepared at high temperatures, high fat consumption, and the excessive usage of salt. Current World Health Organization (WHO) reports also support the hypothesis that above all, red and processed meats are important carcinogens, partly due to nitrites contained in these foods, along with the smoking process. In contrast to this finding, other nutrition aspects (ie, high intake of fiber, and fruit and vegetables) have a cancer protective effect [7-10].

Studies indicate that cancer is low in vegan populations [11,12], but little data exists regarding the effect of a plant-based diet on the progression of diagnosed cancer. However, evidence suggests that a vegetarian or vegan diet provides many other health benefits, such as lower incidence of high BMIs, obesity, and cardiovascular disease [11,12]. The Second World Cancer Research Fund/American Institute of Cancer recommends a mostly plant-based diet and a reduction of red and processed meat in its Research Export Report of 2008 [13], which is also supported by current reports issued by the WHO in 2015 [14]. However, data referring to the therapeutic setting (ie, patients diagnosed with cancer) are still missing. It is of great scientific interest to test the influence of different dietary patterns on the progression of cancer and cancer survival.

Current treatment options for cancer include surgery, radiotherapy, and chemotherapy [1]. Although international research has made progress in the development of new and more specific therapies, treatment options are still limited [15]. Cancer treatments represent a major financial burden on health care systems, patients themselves, and social systems. The main objective of this study is to determine if a reduction or total elimination of animal protein from the diet can positively influence the outcome of an existing cancer and, in addition to standard oncological therapies, increase remission rates.

Furthermore, we aim to estimate the effect size, and enable sample size calculations for future studies. A small number of studies have concentrated on the effect of specific foods, food groups, or food ingredients, such as the effect of soy product consumption in breast cancer patients [16-19], or the effect of reduced red meat intake in patients with colon cancer [20] and prostate cancer [21]. These results are still inconclusive and often show relatively minor effects, likely due to the fact that these studies investigated isolated foods or food groups and not dietary patterns; this study aims to address this limitation.

Cancer patients receive advice from clinicians and their families and friends with respect to nutrition, but studies indicate that patients do not follow this advice over a significant period of time, and improvements based on dietary advice are limited [22,23]. Therefore, it is necessary to test the acceptance and feasibility of different diets, particularly a plant-based diet, in cancer patients. This study hopes to determine if patients who eat a typical omnivore diet can adjust to an alternative diet, and maintain this lifestyle over a period of 6 months or longer. Concerns exist that suggest a vegan or vegetarian diet could lead to a deterioration of health, to tumor progression, or to malnutrition. To address this issue, this study will carefully monitor any deterioration of the patients’ health status.

Previous nutrition and oncological studies have required many professional staff and enormous financial resources. Such studies are often time-consuming for the patients (therefore limiting compliance), necessitating the development of new tools to simplify the process of data collection. To this end, new technologies have been developed and intensively tested [24]. This study will examine the usage of a new online portal as a study platform, in addition to standard medical practices. If this platform proves to be useful, it could be adapted for future studies in the field of nutritional health care.

The validity and significance of self-reported and online-generated data has been questioned [25,26]. Therefore, it is necessary to test these parameters, along with the usability of online data with regard to future applications of research results.

This study aims to address the following issues: (1) to test the hypothesis that the elimination or reduction of dietary animal protein leads to an improved prognosis in tumor patients, as defined by the remission rates, tumor behavior, and relapse-free interval; (2) to estimate the effect size and enable sample size calculations for future studies; (3) to test the feasibility and tolerance of different diets (particularly a vegan diet) in cancer patients, and to assess the effect of a vegan diet on deterioration of health, tumor progression, and malnutrition; (4) to test the online platform as a study platform; and (5) to test the validity of self-reported and online-generated data.

## Methods

### Study Design

This is a prospective, longitudinal, and observational cohort study of cancer patients with four cohorts: (1) omnivore diet, (2) lacto-ovo-vegetarian diet, (3) vegan diet, and (4) other diets (see Table 1). All four cohorts will complete online questionnaires including a baseline assessment and follow-up assessments at 3 and 6 months (Figure 2). At the 12 and 24 month time points, participants will be contacted via email to complete a truncated study questionnaire.

**Table 1 table1:** Definition of dietary patterns.

Cohort	Meat & fish	Milk & dairy products	Eggs	Honey	Plant products
Omnivore diet	+	+	+	+	+
Lacto-ovo-vegetarian diet	-	+	+	+	+
Vegan diet	-	-	-	-	+
Other diets	Those that do not correspond to any of the above				

**Figure 1 figure1:**
[figure not shown]
How patients heard about the study (n=209).

### Eligibility and Recruitment

Patients were eligible for this study if they were diagnosed with cancer, >18 years of age, and were included in a tumor treatment regime or a follow-up program. Exclusion criteria included psychiatric treatment during the previous 3 months, pregnancy, breastfeeding, BMI below 18 kg/m^2^, major difficulties with food intake (eg, swallowing, lack of appetite), and participation in other studies requiring the use of a special diet.

Potential participants were recruited online (via the study website, Facebook, online reports, and television and media reports) and offline (via clinical practices, oncological departments, and associations supporting cancer patients). Recruitment took place between April, 2015 and June, 2016.

### Study Population and Setting

Whenever possible, participants selected one of three defined diets (omnivore, lacto-ovo-vegetarian, or vegan) at baseline. If none of these diets was applicable, participants were classified as having *other diets* (Table 1). Participants were instructed to maintain the chosen diet for 6 months. In addition, respondents were encouraged to continue their prescribed cancer treatment during the study period, and to undergo all recommended follow-up investigations.

Calculation of the required sample size for this study is not possible, as the effect size of the dietary patterns is unknown. Therefore, this study is classified as a pilot study.

The study is being conducted online via a bilingual study website [27]. Registration processes, eligibility assessments, and questionnaires at baseline and follow-ups are all completed online between April, 2015 and December, 2016. Prior to study participation, potential participants performed an online eligibility check (Multimedia Appendix 1), and were asked to provide contact information and a signed patient information and consent form. After registration, participants received an email including their personal login information for the study website, their study identification number, and a link to their baseline questionnaire. Invitations for assessments at 3, 6, 12, and 24 months are delivered by email (Figure 2). If participants do not fill in their questionnaires at the respected time, they are sent reminder emails. In addition to the three main study questionnaires, study participants are asked to report any severe deterioration, unplanned change of their selected diet, or withdrawal from study participation, via online forms (Multimedia Appendix 2).

Ethical approval was obtained from the Ethics Committee of the City of Vienna on February 2nd, 2015 (EK 15-021-VK_NZ).

### Study Groups

At baseline, participants chose one of three defined diet forms for the study period or *other diet* (Table 1). Definitions and nutritional information regarding the diet forms were compiled by a nutritionist, and are available on the study website. All groups were given clear information regarding the avoidance of nutrient deficiencies, and participants were encouraged to continue their prescribed cancer treatment and follow-up investigations. Participants were also advised to have their serum levels of albumin, iron, vitamin D3, and vitamin B12 checked regularly.

### Measures and Evaluation Procedures

The primary outcome of this study is defined as complete tumor remission, and calculated as the rate of complete remissions at 6 months by intention-to-treat (ITT) analysis.

Secondary outcomes include tumor history, further classifications of tumor behavior (complete remission, partial remission, no change, or progression), relapse-free time (in months), survival rates for end stages, previous and current tumor therapies (including tolerance and side effects), comorbidities (eg, high blood pressure, stroke), as well as medications unrelated to the tumor (including dosage and intake plan). The determination of tumor behavior during the study period will be evaluated by two investigators, each using independent radiological and laboratory reports.

Data regarding previous nutritional history, the chosen diet during study participation, acceptance and feasibility of the chosen diet, frequency of dietary pattern change, extent and duration of nutritional changes, and the type and strength of support for nutritional changes will also be assessed. In addition, during baseline and follow-up surveys, adherence to dietary patterns will be cross-referenced by food frequency questionnaires (FFQs), which were specifically adopted for discrimination of plant- and animal-derived foods. Participants were also asked to self-report any unplanned change in diet during study participation. Nutritional status of participants will be evaluated using body weight (kg), BMI (kg/m^2^), laboratory test results (eg, albumin), and questions referring to eating problems. Results referring to nutrition and dietary patterns will be evaluated in terms of change and duration of change in dietary patterns (in months).

Study questionnaires also contain questions referring to quality of life covering the Karnofsky Index, as well as additional dimensions (ie, psychosocial wellbeing, psychosocial support). Online questionnaires were designed to be self-instructive and self-evident (Multimedia Appendix 3). In order to evaluate these parameters, questions pertaining to the study platform and interaction with the study team were also included in the questionnaires. The list of parameters included in the study questionnaire was designed to examine all study objectives, and is detailed in Multimedia Appendix 4.

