### Confounders and Bias

Possible confounders include gender [28] and BMI [29]. Moreover, it is likely that tumor stage and type may influence the results of this study. Therefore, we will examine these factors and adjust our interpretations accordingly. Furthermore, the nature of our website (which highlights the benefits of vegetarian and vegan diets) might attract a population that actively seeks healthy lifestyle habits [27]. Conversely, this group might prefer alternative therapies, and be less compliant to conventional oncological therapies. Therefore, we plan to undertake a subanalysis for treatment groups (oncological treatment followed, oncological treatment rejected, or oncological treatment completed).

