### Statistical Analyses

Statistics regarding safety issues will be performed in July, 2016 and a complete evaluation will be performed in January, 2017. Comparison of dietary groups in regard to primary and secondary end points will be performed as ITT. Data will be analyzed and adjusted for possible confounders (eg, gender, age, tumor type, tumor stage, weight status, accompanying treatment) and stratified by sex, age, type of tumor, tumor staging, and oncological therapy. Changes over time (eg, weight changes) will be analyzed by paired sample tests. Unpaired tests will be used when making comparisons between cohorts. Descriptive statistics will be used to summarize parameters such as comorbidities, oncological therapies, and additional therapies. *P*-values of <0.05 will be considered significant.

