### Bias

This study was performed under free-living conditions, and it was not blinded (open-label design). Study participants chose their dietary pattern by themselves, resulting in participants and study team members being aware of the participants’ dietary pattern. This factor could introduce performance bias (systematic differences between groups in the care that is provided, or due to exposure to factors other than the factor of interest). When choosing their dietary pattern, participants were not manipulated in any way to choose a certain group, and we did not declare the vegan diet as a sufficient treatment for cancer, which might have led to exaggerated expectations.

As of July, 2016, 10 participants with cancer diagnosis and treatment were recruited via a clinical practice, and agreed to participate in the control group (unchanged omnivore diet). These participants have personal contact with study team members, unlike the rest of the included participants. However, all four groups (omnivore, lacto-ovo-vegetarian, vegan, or other) received the same neutral recommendations for avoiding malnutrition.

We did not exclude certain cancer types or stages, and cannot exclude a bias towards certain cancer types prior to the onset of the study. The distribution of these factors (frequency of certain types and stages of cancer) will be analyzed in the complete study evaluation.

Participants were recruited from various countries, and we considered socioeconomic and gender aspects in our study websites, newsletters, questionnaires, and dietary recommendations. Finally, a possible limitation of a web-based study is the attrition phenomenon, which leads to attrition bias. We aimed to minimize this effect using email reminders, and by offering frequent newsletters, blogposts, articles, and a Facebook site for the study.

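### The primary outcome, complete remission at 6 months, is not limited to participants with tumor present at baseline, so it mixes entry status with any diet effect.

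*Protocol article*

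**What the plan says.** Under Measures and Evaluation Procedures, the primary outcome is complete tumor remission, "calculated as the rate of complete remissions at 6 months by intention-to-treat (ITT) analysis". No condition on disease status at baseline is attached. The same section lists a four-class scale of tumor behavior as a secondary outcome (complete remission, partial remission, no change, progression), to be judged by two investigators from radiological and laboratory reports. It also lists "relapse-free time (in months").

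Under Eligibility and Recruitment, patients qualify if they "were included in a tumor treatment regime or a follow-up program". The exclusions concern psychiatric treatment, pregnancy, breastfeeding, low BMI, eating difficulties and participation in other diet studies. None concerns remission. The Bias section adds: "We did not exclude certain cancer types or stages".

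On allocation, the Bias section states: "Study participants chose their dietary pattern by themselves".

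Statistical Analyses plans a comparison by ITT, "adjusted for possible confounders (eg, gender, age, tumor type, tumor stage, weight status, accompanying treatment"), and stratified by sex, age, tumor type, staging and oncological therapy. Confounders and Bias adds a subanalysis by treatment group: "oncological treatment followed, oncological treatment rejected, or oncological treatment completed". Baseline remission status is not named as a restriction, an adjuster or a stratum.

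**The concern.** The stated objective is to learn whether less animal protein in the diet can raise remission rates. Only a participant who has tumor at entry can newly reach remission. The plan applies the remission rate to everyone who chose a diet, and the protocol itself foresees participants who may be tumor-free at the start: follow-up patients are eligible, a treatment-completed group is named, and relapse-free time is an outcome.

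Two things are at stake. First, participants already in remission dilute any real effect in those with tumor. This happens even if the cohorts are perfectly balanced. Second, participants choose their diet, and Confounders and Bias expects the website to attract a particular population. The share already in remission may therefore differ between cohorts, and such a difference would appear in the primary comparison as if it were an effect of diet.

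The study calls itself a pilot, but one stated product is an effect size for planning later trials. A diluted or biased estimate undermines that purpose directly.

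**Working it through.** The article states no remission rate, expected effect or sample size, so there is no design figure to reproduce. What follows shows the mechanism. Every input is an assumption.

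**Notation**
- b: share of a cohort already in complete remission at baseline.
- s: share of those still in remission at 6 months, assumed 90% to 95%.
- q: share of those with tumor at baseline who newly remit by 6 months, assumed 10% to 20%.
- s and q are the same in both cohorts, meaning no diet effect.

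**Reading A: the outcome is remission status at 6 months**

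Rate = b × s + (1 − b) × q. The difference between two cohorts is then (b1 − b0) × (s − q).

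Over the assumed ranges, s − q runs from 0.90 − 0.20 = 0.70 to 0.95 − 0.10 = 0.85. The spurious difference is:
- 10-point baseline imbalance: 7 to 8.5 points
- 20-point imbalance: 14 to 17 points
- 30-point imbalance: 21 to 25.5 points

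Worked case with s = 95% and q = 10%:
- b = 30%: 0.30 × 0.95 + 0.70 × 0.10 = 35.5%
- b = 50%: 0.50 × 0.95 + 0.50 × 0.10 = 52.5%
- difference: 17.0 points with no diet effect

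In this case an unadjusted two-sided 5% test of two proportions would be significant in about 26%, 40% and 53% of studies with 30, 50 and 70 participants per group (assumed sizes). With the two shares exchanged, the difference is −17.0 points. With equal shares it is zero.

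**Reading B: the outcome is new remissions, divided by everyone in the cohort**

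Rate = (1 − b) × q. The difference is −(b1 − b0) × q. A 20-point imbalance gives −0.20 × 0.10 = −2 points to −0.20 × 0.20 = −4 points. The bias is smaller in points and opposite in sign to Reading A. The sign of the bias therefore depends on a choice between readings that the article leaves open.

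**Dilution, the same under both readings**

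Suppose b is equal in both cohorts and diet changes q by d but leaves s unchanged. The observed effect is (1 − b) × d.
- d = 10 points, b = 50%: 0.50 × 10 = 5 points
- d = 15 points (10% against 25%): 10.5, 7.5 and 4.5 points for b = 30%, 50% and 70%

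**With the outcome restricted to participants with tumor at baseline**

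The no-effect comparison becomes q against q, a difference of zero in every scenario above, and a true d is seen undiluted.

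**The case against.** The strongest case on the other side has four parts.

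*The text does not say that patients in remission count as successes.* The tumor-behavior scale resembles a response scale, and a participant who is tumor-free throughout might be classed as unchanged. This stands: the reading as 6-month status is not certain. It does not rescue the outcome, because such a participant then stays in the ITT denominator without being able to remit (Reading B).

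*The planned analysis already addresses imbalance.* The list of adjusters is introduced as examples and so is open. The comparison is stratified by staging and oncological therapy, and a subanalysis separates participants whose treatment is completed. This stands in part: it would remove some of the imbalance, and the figures for Reading A, which are unadjusted, may overstate what is left. But stage is not remission status, and completed treatment does not establish complete remission. No adjustment enables a participant in remission to remit anew.

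*The full protocol or analysis plan may define the set at risk.* It may. The article nevertheless states both the outcome and the ITT rule, and a restriction elsewhere would change what is stated here.

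*The magnitudes are assumed.* This stands in full. No baseline remission share is given, overall or by diet.

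A reader might go further and infer that the outcome reflects only who chose each diet, that the bias favors the plant-based cohorts, or that the study cannot answer its question. The documents support none of these. The rate mixes entry status with any diet effect. The direction of the bias is unknown. The planned adjustment, the tumor-behavior classes and relapse-free time still carry information.

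**Conclusion.** The point holds as a defect in the definition of the primary outcome. As written, the outcome is applied to a population that can include people who cannot newly remit. If any such people are enrolled, a true effect on new remission is diluted under either reading. If their share differs between the self-selected cohorts, the comparison is also biased.

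The size cannot be determined from the documents. Under the assumed 90-95% persistence, 10-20% new remission and no diet effect, a 20-point imbalance would produce about 14 to 17 points of spurious unadjusted difference in 6-month status. With equal shares and half already in remission, a true 10-point effect would show as 5. The dilution figure also assumes that diet does not alter persistence of remission. If it does, a 6-month status rate would combine prevention of relapse with induction of remission, which is a further reason to separate the two groups.

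**What to change.** Before the complete evaluation, which Statistical Analyses schedules for January 2017:

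1. Classify each participant's disease status at baseline from the tumor history and the reports, preferably by the two investigators who already judge tumor behavior and without knowledge of the diet chosen. State how participants with unclassifiable baseline status are handled.
2. Define the primary outcome as new complete remission at 6 months among participants with tumor present at baseline, keeping all of them in the diet cohort they chose.
3. Analyse participants already in remission for relapse, timed from the baseline survey.

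As a minimum, stratify the primary comparison by baseline remission status and report the strata separately. Stratification deals with the imbalance, but a result pooled over strata would still be diluted.

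The cost is some classification work and a smaller primary set. The loss is not trivial: Recruitment and Dropout Rates reports 33 completers of the 6-month survey as of May 2016, spread over up to four cohorts. The change also depends on usable baseline reports, and the article does not confirm that these exist for everyone. Ordinary confounding from self-selected diet remains after the change and still needs the planned adjustment.

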### Data Safety

Online data safety was a priority in the development of this study, and we strictly separated participants’ personal data (used for communication) from anonymous health/disease related data. To ensure anonymity, each participant received a personal login and study identification number. Administrative (personal) data were collected and stored on servers with enhanced security features. Password-restricted logins and Secure Sockets Layer-encrypted data transmission were used, and host server providers were required to sign a contract according to the German Bundesdatenschutzgesetz [30] to guarantee state-of-the-art handling, storage, and deletion of personal data. Health-related data were collected and hosted at Survey Monkey [31], using anonymous study questionnaires on a server compatible with the Health Insurance Portability and Accountability Act.

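### The primary outcome is an investigator classification with no stated masking to diet, in a study whose team knows the diet, and the resulting detection bias is not addressed

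*Protocol article*

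**What the plan says.** Measures and Evaluation Procedures sets the endpoint: "The primary outcome of this study is defined as complete tumor remission, and calculated as the rate of complete remissions at 6 months", analysed by intention to treat. The secondary outcomes in the same section include "further classifications of tumor behavior (complete remission, partial remission, no change, or progression", so complete remission is the top category of the tumor behavior scale. On who assigns the category, the section says: "The determination of tumor behavior during the study period will be evaluated by two investigators, each using independent radiological and laboratory reports". It does not say whether these investigators are kept unaware of diet.

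The Bias section of the Discussion says of the study that "it was not blinded (open-label design". It describes diet as self-chosen, "resulting in participants and study team members being aware of the" participants' dietary pattern. The consequence it draws is: "This factor could introduce performance bias". It goes on to discuss the ten clinic-recruited omnivore controls who have personal contact with the team, the mix of cancer types and stages, and attrition. Confounders and Bias covers patient characteristics, the kind of person the website attracts, and treatment groups. Neither section mentions bias in judging the outcome.

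Three further places bear on a remedy. Data Safety separates personal data, "used for communication) from anonymous health/disease related data", and gives each participant a study identification number. The Appendix list says that participants can upload medical reports in the login area. Statistical Analyses places the complete evaluation in January 2017.

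**The concern.** The study takes all cancer types and stages, and the evidence on tumor response comes from radiological and laboratory reports. Turning such reports into complete remission or something less takes judgement in some cases. The hypothesis is directional: less animal protein, better prognosis. Confounders and Bias acknowledges that the study website presents vegetarian and vegan diets favourably. If a rater knows the diet, doubtful cases can drift in the hypothesised direction.

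Such an error depends on exposure. The adjustment and stratification in Statistical Analyses work on sex, age, tumor type, stage, weight status and treatment. They cannot correct an outcome recorded differently according to diet.

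The pilot is also meant to supply an effect size for later sample size calculations (Introduction, aim 2). A shift in the estimate would carry into those calculations whether or not the pilot's own test is significant.

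**Working it through.** **Step 1: the text.** The article has no figure to reproduce on this point, so the sections are set side by side.

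- Who decides the primary outcome: two investigators, through the tumor behavior categories (Measures and Evaluation Procedures).
- What they use: radiological and laboratory reports (same section).
- Masking of these two: none stated.
- Knowledge of diet: study team members have it (Bias).
- Bias inferred by the article: performance bias only (Bias).

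Performance bias concerns differences in care or other exposures. Detection bias concerns how the outcome is determined. The article states the fact that gives rise to both and names only the first.

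**Step 2: illustrative size.** The article gives no remission rates, cohort sizes or rater error rates. All inputs here are assumptions.

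- p, true complete remission in both cohorts: 30% to 50%.
- d, share of non-remitters wrongly called complete remission in one cohort only: 2% to 20%.

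Apparent rate in the affected cohort: q = p + (1 − p)d. Spurious difference: Δ = (1 − p)d.

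| p | d | Δ |
|---|---|---|
| 0.50 | 0.02 | 0.50 × 0.02 = 0.010 |
| 0.30 | 0.02 | 0.70 × 0.02 = 0.014 |
| 0.50 | 0.10 | 0.50 × 0.10 = 0.050 |
| 0.30 | 0.10 | 0.70 × 0.10 = 0.070 |
| 0.50 | 0.20 | 0.50 × 0.20 = 0.100 |
| 0.30 | 0.20 | 0.70 × 0.20 = 0.140 |

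The range is 1 to 14 percentage points and does not depend on sample size.

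**Step 3: effect on the test.** For n per cohort and a two-sided 5% test (the article gives 0.05 but no sidedness), SE = √{[p(1 − p) + q(1 − q)]/n}, and the rejection rate is Φ(Δ/SE − 1.96) + Φ(−Δ/SE − 1.96).

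Worked case with p = 0.30, q = 0.44, n = 60: SE = √[(0.2100 + 0.2464)/60] = 0.0872, Δ/SE = 1.605, rejection rate 0.362.

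The values of n split counts in the preliminary recruitment section equally over four cohorts, which is also an assumption: 242 registered (242/4 ≈ 60), 138 first surveys completed (138/4 ≈ 35), 33 six-month surveys completed (33/4 ≈ 8).

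| n per cohort | p = 0.5, d = 0.02 | p = 0.3, d = 0.02 | p = 0.5, d = 0.10 | p = 0.3, d = 0.20 |
|---|---|---|---|---|
| 60 | 5.1% | 5.3% | 8.5% | 36.2% |
| 35 | 5.1% | 5.2% | 7.0% | 23.2% |
| 8 | 5.0% | 5.0% | 5.5% | 9.0% |

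The normal approximation is rough at n = 8. The false-positive rate runs from barely above nominal to 36%, depending wholly on the assumed inputs.

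**The case against.** The strongest reply has four parts.

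*The raters are not stated to know the diet.* The Bias section speaks of study team members in general, and no sentence says that the two investigators see the diet when rating. A condensed article may leave reader procedures to the full protocol. It is right that the raters' knowledge of diet is an inference, although the ordinary one. But the article does more than stay silent: it affirms team awareness and draws an incomplete conclusion from it. The absence of response criteria or a disagreement rule is not counted as a defect here, since a fuller document may hold them.

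*Safeguards exist.* There are two raters working from documented radiology and laboratory findings, and only the boundary of complete remission affects the primary outcome. A patient with reported progression is unlikely to be called a complete remission. This stands as a reason to expect a smaller bias, and is why the range starts at 2% over-calling. It limits the bias without excluding it.

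*The wording on independent reports may be a strength.* A reader might infer that the two investigators see different material. The phrase can equally mean reports produced outside the study. It is ambiguous, and nothing here rests on it.

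*Other threats are larger.* Self-selected diet, mixed tumor types and stages, and a preliminary dropout rate of 67.3% may distort the comparison more. That is a fair point on priority. It is no reason to leave an inexpensive correction undone.

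A reader might also infer from Data Safety that the data structure already masks the raters. It does not show that: it separates identity from health data, whereas diet and tumor items both sit in the study questionnaires.

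**Conclusion.** The point holds as a should-fix. The primary outcome depends on an investigator judgement for which no masking is stated, in a study that declares its team aware of diet, and detection bias is not recognised. This rests on reading the two investigators as part of that team.

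The size cannot be derived from the article. The spurious difference of about 1 to 14 points rests on assumed over-calling of 2-20% of non-remitters in one cohort and assumed true remission of 30-50%. The 36% false-positive rate should not be quoted as an expected figure: it combines the heaviest assumed over-calling with the largest assumed cohort. Nothing in the article shows that biased rating has occurred.

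Masking is feasible, because participants have study numbers and medical reports are uploaded separately. The article does not show that it is already in place.

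**What to change.** Amend Measures and Evaluation Procedures to say that:

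- the two existing investigators each rate the same set of reports for every study ID, independently of each other;
- they have no access to the diet selection, the food frequency questionnaire or the diet-change forms, and mentions of diet in the reports are redacted beforehand;
- disagreements are settled, still without diet information, before the cohort variable is merged with the ratings;
- where possible, the raters are not the team members in personal contact with the ten omnivore controls.

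Add detection bias to the Bias section, and say there what masking does and does not cover.

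No extra reader and no further patient contact are needed. The cost is clerical: exporting reports by study ID and redacting names and diet remarks. The article does not describe such an export, so the route has to be set up. On the article's own timetable, the change belongs before the complete evaluation in January 2017.
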